**Safety requirements**	

Hearing	*both occupations:*
	Audiogram [20]

Eyesight	Signalling questions and eye test at 5 m [21]

Working at heights	Signalling questions (weariness, alertness)

Psychological vigilance	*both occupations:*
	Screening questionnaires:
	Need for recovery after work [22,23]
	Distress [24]
	Depression [25,26]
	Anxiety [25,26]
	Post-traumatic stress disorder [27]
	Risky alcohol consumption [28]
	*supervisors only:*
	Screening questionnaire burn-out [29]

**Health requirements**	

**Working with hazardous substances**	

Skin	*both occupations:*
	Signalling questions skin
	*bricklayers only:*
	Screening questionnaire hand dermatitis [30]

Lungs and airways	*both occupations:*
	Signalling questions skin, lungs and airways [31]
	Spirometry [31]
**Cardiometabolic health**	*both occupations:*
	Risk score cardiometabolic diseases [32]
	Cardiovascular risk profile [33]

**Work functioning**	*both occupations:*
	First 5 questions of the work ability index [34-36]
	*supervisors only:*
	Job-specific addition with mental requirements

### Care as usual

CAU aims at detecting signals of work-related health problems and risk factors. The worker fills in a questionnaire and a physician's assistant carries out biometry measurements. The biometry measurements of both the job-specific WHS and CAU are identical. The questionnaire covers several topics including health, perceptions of work and risk factors at work. Neither scale scores nor cut-off points are calculated, except for work ability. The questionnaire used in CAU is identical for all occupations, and no protocol exists for analysing the results. The OP discusses the results of both the biometry and the questionnaire with the worker in a 20-minute consultation. No structured protocol exists to facilitate the OP in their counselling. A report of the results is sent to the home address of the worker afterwards.

### Training OPs and ergonomists

The OPs and ergonomists who carry out the job-specific WHS participate in a half-day training course. This training course consists of an explanation of the background and development of the job-specific WHS. OPs and ergonomists will be instructed on their protocol to be followed in the WHS and the role of the ergonomist in the WHS.

We consider the procedures and guidelines imposed by Arbouw for carrying out the WHS as care as usual. However, from the pilot study, it became clear that several barriers and ignorance exist regarding these procedures. Therefore, the OPs in the control group receive a two-hour class in order to train them to carry out the WHS according to the guidelines and procedures required by Arbouw.

#### Sample size and assignment

The sample size is based on detecting a difference in activities or interventions undertaken by the worker in the six months after they have attended their WHS. No information on this is available from literature. From the registered activities and interventions in the Arbouw-database, we expect 10% of the workers in the control group to undertake an activity registered by the OP. We have decided that an absolute increase of 20% in interventions undertaken by the workers is a relevant difference. For an increase of 20% (from 10 to 30%) with alpha 0.05 (two-tailed) and a power of (1-beta) = 0.80, power calculation using the Nquery Advisor software results in 75 workers per group. However, we expect a small effect at the level of the OP (ICC = 0.01). Every OP will treat ~15 workers. This results in a design effect of 1.14 ((1+(N-1)*ICC) and an adjusted sample size of 86 per group, divided over at least 6 OPs [16]. With an expected loss to follow-up of 20% and an initial attendance of 50% at the OHS, we must invite 206 workers per group (103 bricklayers, 103 supervisors).

We do not expect major differences between the various offices of a single coordinating OHS. No restrictions or matching criteria were imposed.

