**Methods/Design:**

The ongoing study of bricklayers and supervisors is a nonrandomised trial to compare the outcome of an intervention (job-specific WHS) group (n = 206) with that of a control (WHS) group (n = 206). The study includes a three-month follow-up. The primary outcome measure is the proportion of participants who have undertaken one or more of the preventive actions advised by their occupational physician in the three months after attending the WHS. A process evaluation will be carried out to determine context, reach, dose delivered, dose received, fidelity, and satisfaction. The present study is in accordance with the TREND Statement.

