## Methods/design

### Dutch context

In the Netherlands, employers are obliged to offer their employees a medical examination, as stated in Article 18 of the Dutch Working Circumstances and Occupational Health and Safety Act [12]. Employees in the construction industry are invited for such a medical examination once in every four years (when they are under the age of 40) or every two years (when they are over 40 years old). This examination is part of their collective labour agreement. Arbouw (the Health and Safety Institute for the Dutch construction industry) provides this service for all employees in the construction industry. Employees are invited to an Occupational Health Service (OHS) near their place of residence. Attending the periodic medical examination is voluntarily. At the time this study was prepared, the attendance rate was 47% [13]. In the collective labour agreement of the workers is recorded that 1) research is performed at the OHS under the authority of Arbouw and 2) the information collected during the medical examinations can be used for research purposes. When attending their medical examination the workers are reminded in writing of this agreement and they can choose whether or not to participate voluntarily. The workers are aware of the fact that by participating they give the researchers written consent to use their information anonymously for research purposes.

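### The 206 invitations per group do not deliver the 86 analysable workers that the sample size section requires: its own rates need 215, and 206 gives about 82 (minor)

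*Protocol article*

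**What the plan says.** All the inputs are in the protocol article, mostly under *Sample size and assignment*.

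- Test and effect: "For an increase of 20% (from 10 to 30"%, "with alpha 0.05 (two-tailed) and a power of (1-beta) = 0.80".
- Unadjusted size: "power calculation using the Nquery Advisor software results in 75 workers per group".
- Clustering: "we expect a small effect at the level of the OP (ICC = 0.01"), with about 15 workers per occupational physician (OP). The design effect is 1.14, giving "an adjusted sample size of 86 per group, divided over at least 6 OPs".
- Recruitment: "With an expected loss to follow-up of 20% and an initial attendance of 50% at the OHS, we must invite 206 workers per group", split into 103 bricklayers and 103 supervisors. The formula for this last step is not shown.

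Two other places bear on the point. Under *Dutch context* the article reports "At the time this study was prepared, the attendance rate was 47"%. The *Methods/Design* part of the abstract describes the comparison as an intervention "group (n = 206) with that of a control (WHS) group (n = 206").

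**The concern.** The section builds up a requirement of 86 workers per group and converts it into a number of invitations, which is the figure the recruiting offices act on. If that conversion is wrong, the study is set up to miss its own stated target even when attendance and retention go exactly as assumed.

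The abstract adds a labelling problem. A reader who sees only the abstract would take 412 workers to be compared. The primary outcome is defined relative to workers who attended, which is about half that number on the plan's own rate, and fewer after loss to follow-up.

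**Working it through.** **Reproducing the plan's steps**

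1. Design effect: 1 + (15 − 1) × 0.01 = 1.14. This reproduces.
2. Adjusted size: 75 × 1.14 = 85.5, rounded up to 86. This reproduces.
3. Invitations: 86 × 1.2/0.50 = 206.4, which matches the stated 206.

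**The conversion that the stated rates imply**

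If 20% of attenders are lost, 80% remain, so the required number must be divided by 0.80 and then by the attendance rate:

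- From 86: 86/0.80 = 107.5 attenders; 107.5/0.50 = 215 invitations. Rounding attenders up to 108 first gives 216.
- From the unrounded 85.5: 85.5/0.80/0.50 = 213.75, so 214. Rounding does not explain the gap.

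**Forward check of 206**

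- Attending: 206 × 0.50 = 103.
- Analysable: 103 × 0.80 = 82.4, which is 3.6 below 86 (3.6/86 = 4%).
- To keep 86 from 206 invitations, loss would have to be 1 − 86/103 = 16.5%, or attendance 86/0.80/206 = 52%. The article states neither.

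**Power at the sizes concerned**

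This is a two-sided test at 0.05 of 10% against 30%. The effective size per group is n divided by 1.14. With effective size m, uncorrected power is Φ{[0.20√m − 1.96√(2 × 0.20 × 0.80)]/√(0.09 + 0.21)}. For the continuity-corrected figure, m is replaced by m(1 − 1/(0.20m))².

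| Analysable per group | Effective size | Power, uncorrected | Power, corrected |
|---|---|---|---|
| 86 (target) | 75.4 | 0.87 | 0.83 |
| 82.4 (206 invited, 50% attend) | 72.3 | 0.86 | 0.81 |
| 77.5 (206 invited, 47% attend; sensitivity only) | 67.9 | 0.84 | 0.78 |

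Power holds at 82 because the stated 75 has some margin. The standard formulas for these inputs need 62 per group without continuity correction and 72 with it.

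**Sensitivity to attendance**

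At 47%, 206 × 0.47 × 0.80 = 77.5 analysable. Reaching 86 would take 86/0.80/0.47 = 228.7, so 229 invitations.

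**The case against.** **The shortfall changes nothing of substance.** This largely stands. On the plan's own rates the gap is under four workers per group, and power stays at or just above 0.80 by either calculation. A reader might infer that the trial is underpowered, but the figures do not support that. The only value below 0.80 needs both 47% attendance and a continuity correction, whereas the planned analysis of binary outcomes is a two-level logistic model, to which that correction does not belong. Holding the design effect at 1.14 is also slightly severe: with six OPs and 77.5 workers, clusters of about 13 give a design effect near 1.12 and corrected power of about 0.79.

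**50% attendance is a legitimate planning value.** This stands too. It is tempting to read 50% against 47% as a second arithmetic error. The 47% is reported in a paragraph on construction employees in general, not for bricklayers and supervisors at the selected offices. The choice of 50% is unexplained and mildly optimistic, but it is an assumption, so 47% serves here only as a sensitivity check.

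**The faulty route is inferred.** This is correct, because the article prints no formula. From the stated 86, adding 20% returns 206 and dividing by 0.80 does not. Another route exists: the continuity-corrected 72 would give 72 × 1.14/0.80/0.50 = 205.2, or 206 rounded up. The article, however, states 75 and 86. Whatever the route, 86, 20%, 50% and 206 cannot all hold.

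**Losses might be counted as no action taken.** The primary outcome is expressed relative to all attenders, so the denominator could be 103. But the sample size section itself inflates for loss to follow-up and so treats losses as reducing the sample. Even on that reading, 206 is not the size of a compared group.

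**The main text already says that 206 are invited.** It does, so the abstract is a labelling fault that a full reading resolves. It still misstates the size of the comparison for anyone who reads only the abstract.

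**Conclusion.** Wrong as written, and minor. On the section's own inputs the required number is 215 invitations per group, not 206. The stated 206 yields about 82 analysable workers per group against a target of 86. This rests only on the stated 86, 20% loss and 50% attendance, with loss taken as a fraction of attenders. That 20% was added rather than divided out is a strong inference, not something the article says.

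The conclusion stops there. The planned 0.80 power is preserved at 82 workers, given the stated event rates and a design effect of 1.14, so this is not a finding of inadequate power. The abstract's use of 206 as the compared group size conflicts with the main text, where it is the number invited.

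**What to change.** Make one of two changes under *Sample size and assignment*:

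- Correct the invitation number to 215 per group (216 if it is to split evenly, 108 per occupation). This is 9 or 10 more invitations per group. It may not be possible: the *Limitations* section says that numbers depend on how many bricklayers and supervisors are eligible for invitation, and that the largest offices have already been selected.
- Keep 206 and state that about 82 analysable workers per group are expected, with power of about 0.81 (continuity-corrected) or 0.86 (uncorrected). This costs one sentence and is feasible in any case.

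Whichever is chosen, print the formula for the loss and attendance steps. A short note could add that 47% attendance would leave about 77 analysable workers per group, with power of about 0.78 corrected or 0.84 uncorrected.

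In the abstract, label 206 as the number invited per group, and give the planned attending (about 103) and analysed (about 82) numbers beside it. If the invitation number is raised, update all three figures to match.

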### Measurements

Baseline data are obtained from the results of the job-specific WHS, CAU, the additional questionnaires to be filled in by the worker and OP and the official registration system for the OP. Two months after baseline, a follow-up measurement takes place; three months after baseline, a second follow-up measurement takes place. At all measurements occupation and any possible worker compensations such as early retirement or partial disability are queried.

Follow-up data are obtained from questionnaires to be filled in by the worker and the OP and the official registration system used by the OP to administer the planned and executed activities.

#### Primary outcome

The primary outcome variable (measured at the two-month and three-month follow-ups) compares the number of workers who have undertaken one or more preventive actions advised by their OP after attending their WHS relative to the total number of workers who attended their WHS. The outcome measure 'preventive action' is dichotomised into 'did undertake preventive action' for the workers who did make use of one or more adequate preventive actions and 'did not undertake preventive action' if no preventive action was undertaken.

Preventive actions are classified by the OP into the following domains: i) more detailed examination of the complaint or risk factor, for example, a visit to the OP, general practitioner or specialist, or a workplace visit); ii) individual preventive actions aimed at reducing risk factors or increasing work capacity (for example, visiting a physical therapist, participating in a lifestyle program) and iii) preventive actions taken at the technical or organisational level (for example workplace adjustments or training and education).

#### Secondary outcomes

Secondary outcome parameters are i) the proportion of workers with suggested preventive actions of the OP in their worker reportage (number of workers with one or more preventive actions in their report relative to the number of workers that attended their WHS); ii) the number and type of preventive actions (job-specific or general health) advised by the OP; iii) the number and type of preventive actions undertaken (job-specific or general health) by the worker and iv) work ability. Furthermore, the direct costs per worker for the funder of the WHS will be determined.

#### Process evaluation

In addition to the effect evaluation, the process of the intervention will be evaluated. The following components of the process will be evaluated: context, reach, dose delivered, dose received, fidelity and satisfaction [17].

Contextual aspects such as the political and economic environment may influence intervention implementation. Contextual factors will be monitored during data collection by questioning OPs and workers on economic recession, organisational or financial changes (for example, at the level of the OHS) and factors related to circumstances concerning the individual worker such as changes at the level of their employer.

Reach will be expressed as the attendance rate of the workers at their OHS. Attendance will be defined as the number of workers who attended their WHS relative to the number of workers who were invited by the OHS at baseline.

The dose delivered is a function of efforts of the OPs and other occupational health professional. Dose delivered will be defined as the number of preventive actions or follow-up arrangements provided (registered) to the worker by the OP at two or three months relative to the number of workers with an officially registered or noted follow-up appointment in the worker's report at baseline.

The dose received is the extent of engagement of the workers with the intervention. Dose received will be defined as the number of workers who undertake a prevention action at two or three months after their WHS relative to the number of workers who were advised to take a prevention action by the OP at baseline. In addition, we will assess the number of workers who intended to take a prevention action after their WHS at baseline relative to the number of workers who were advised to take a prevention action by the OP.

Fidelity is the extent to which an intervention is delivered as planned. We will assess the integrity and quality of the job-specific WHS by assessing protocol adherence. We developed performance indicators and will score these as 'sufficient' or 'insufficient' based on the workers' reportage and questionnaires at the two-month and three-month follow-ups. A total score will be calculated. Fidelity will be expressed as the frequency of total scores per group and per OP. Furthermore, we will ask the workers to what extent the WHS provided them more knowledge on their own health status and work ability.

The satisfaction of the workers with both CAU and the intervention will be evaluated in three ways. All workers will be asked to rate on a scale from 1 to 10 (not satisfied to very satisfied): 1) the WHS as a whole (at baseline); 2) the advised preventive actions (at baseline) and 3) the effect of the preventive actions on their health status and work ability (at the two-month and three-month follow-ups).

### Statistical analysis

The baseline data and the primary and secondary parameters will be presented using descriptive statistics. The following characteristics at baseline will be compared between the intervention and control groups: occupation, work experience in years in construction and in the current occupation, work hours per week and any possible worker compensations such as early retirement or partial disability. Furthermore, these characteristics will be compared overall and by study condition in those lost to follow-up and those retained. Moreover, the age and occupation of the study population at baseline and target population (all invited by the OHS) will be compared. Differences in continuous outcome measures will be tested with an independent samples T-test, differences in proportions will be tested with a Chi-Square test.

The effectiveness of the job-specific WHS on the primary and secondary outcome measures will be analysed on the individual level. First, data for the whole group will be analysed irrespective of the occupation of the worker. Second, subgroup analyses will be performed among the bricklayers and supervisors. For all analyses, a significance level of 0.05 will be applied. Workers with the same OP tend to be more homogeneous than workers with different OPs. Therefore, a two-level logistic regression model with workers at level 1 nested within OPs at level 2 will be used to analyse the binary data. The SPPS Advanced Statistics 19 software will be used to perform the logistic multilevel analysis by using a Generalised Linear Mixed Model (GLMM).

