### Study population and recruitment

The research population includes all workers with the occupation bricklayer or supervisor who are invited by the OHS. Workers are eligible to participate when they are i) primarily working as a bricklayer or construction supervisor; ii) male; iii) able to read, speak and write Dutch sufficiently well and iv) not planning to leave their occupation in the three months after inclusion due to resignation or (early) retirement. Because both occupations consist primarily of men, we include only men.

The study population is recruited through the participating OHS. The workers, who are invited at the offices where the job-specific WHS is implemented, are informed by a letter about the innovation at their OHS. Then, concurrent procedures are performed for both the control and intervention groups: all workers are asked to confirm their attendance, and if necessary, another date or time is arranged. When a worker does not show up without cancelling, the OHS will try to follow-up by phone to make a new appointment if desired by the worker.

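### Participants are compared with all invited workers, a group that contains them, and the only tests named assume separate samples, so a non-significant result is weak evidence against small to moderate selection

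*Protocol article*

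**What the plan says.** The first paragraph under Statistical analysis lists the planned baseline comparisons: intervention against control, workers lost against workers retained, and finally the participants against the target population: "the age and occupation of the study population at baseline and target population (all invited by the OHS) will be compared". The next sentence, which closes that paragraph, names the tests: "Differences in continuous outcome measures will be tested with an independent samples T-test, differences in proportions will be tested with a Chi-Square test". The following paragraph adds: "For all analyses, a significance level of 0.05 will be applied".

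Other sections show that the first group lies inside the second. Study population and recruitment says: "The research population includes all workers with the occupation bricklayer or supervisor who are invited by the OHS". Sample size and assignment arrives at 206 invitations per group from "an expected loss to follow-up of 20% and an initial attendance of 50% at the OHS". Dutch context gives an attendance rate of 47% at the time of preparation. Process evaluation defines reach as attenders divided by invited.

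The article mentions neither an adjustment for the overlap nor a comparison with those who did not take part.

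**The concern.** Both named tests assume that the two groups share no members. Here roughly half of the comparison group is the study group itself. The two means are positively correlated, so the usual standard error of their difference is too large and the test is conservative.

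A conservative test does little harm when one hopes to show a difference. In this check the comfortable result is no difference, and that is the result the error favours. This is the only planned comparison of the characteristics of those who took part with those invited. Reach gives a rate and does not describe who came, and the comparison of lost with retained workers concerns a later stage. Selection is plausible: attendance is voluntary, about half do not come, and workers at the intervention offices are told about the innovation by letter before they confirm attendance.

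**Working it through.** **Inputs.** Attendance of 50% and 206 invited per group (Sample size and assignment); 47% attendance (Dutch context); two-sided alpha of 0.05. The article gives no error rate or power for this comparison.

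**The plan's own figure.** 75 × 1.14 = 85.5, rounded to 86. Then 86 × 1.2 / 0.5 = 206.4, which reproduces the 206 invited per group, 412 in total.

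**Formulas.** Let N be the number invited, f the participating fraction, s a common SD, and Δ the mean of participants minus the mean of non-participants.

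- Participants minus all invited = (1−f)Δ.
- True variance = (1−f)² s² [1/(fN) + 1/((1−f)N)] = s²(1−f)/(fN).
- Variance used by the independent-samples formula = s² [1/(fN) + 1/N] = s²(1+f)/(fN).
- The standard error is therefore overstated by r = sqrt((1+f)/(1−f)), whatever N is.

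**Numbers at f = 0.50, N = 412, s = 1.** SE used = sqrt(1/206 + 1/412) = 0.0853. True SE = sqrt(1/206 − 1/412) = 0.0493. r = 1.73, so the effective critical value is 1.96 × 1.73 = 3.39. Real level = 2(1 − Φ(3.39)) = 0.0007. Where a correct test has 80% power, its expected z is 1.96 + 0.84 = 2.80, and the planned test has power Φ(2.80 − 3.39) = 0.28.

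| f | r | Real level | Planned power where a correct test has 80% |
|---|---|---|---|
| 0.50 | 1.73 | 0.07% | 28% |
| 0.47 | 1.67 | 0.11% | 32% |
| 0.40 | 1.53 | 0.28% | 42% |
| 0.20 | 1.22 | 1.6% | 66% |

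**Simulation at f = 0.50.** 8,000 runs per t-test setting and 40,000 per chi-square setting; equal SDs, equal numbers of both occupations invited, no clustering by physician. N = 412 pools both groups; N = 206 is one group alone. The correct test compares participants with non-participants.

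| Selection | N | Planned test | Correct test |
|---|---|---|---|
| Age, 0.2 SD | 412 | 9% | 53% |
| Age, 0.3 SD | 412 | 36% | 87% |
| Age, 0.4 SD | 412 | 74% | 98% |
| Age, 0.5 SD | 412 | 95% | >99% |
| Age, 0.3 SD | 206 | 10% | 57% |
| Age, 0.5 SD | 206 | 55% | 95% |
| Age, 0.8 SD | 206 | 99% | 100% |
| Attendance by occupation, 45% vs 55% | 412 | 9% | 54% |
| Attendance by occupation, 43% vs 57% | 412 | 29% | 82% |
| Attendance by occupation, 40% vs 60% | 412 | 75% | 98% |
| Attendance by occupation, 35% vs 65% | 412 | >99% | 100% |

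By formula, 80% power needs an age difference of 0.276 SD with the correct test and 0.417 SD with the planned one at N = 412; at N = 206 the values are 0.390 and 0.590 SD.

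**The case against.** **The test is inferred.** The sentence naming the tests speaks of outcome measures, and age and occupation are not outcomes. The secondary outcomes include quantities that could be treated as continuous (work ability, numbers of actions), so the sentence has a literal object without age. The section also opens by promising descriptive statistics, and a fuller plan may exist. This stands as a caveat: if the comparison is purely descriptive, the level and power figures do not apply. The sentence does, however, close a paragraph of baseline comparisons, effectiveness is taken up only in the next paragraph, and no other test is offered for this comparison. Applying it here is the natural reading. Nor is the point one of omission, because comparator and tests are both stated and do not fit together.

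**The fraction may be below one half.** Eligibility limits and voluntary research participation may remove some attenders from the study population, and all invited could extend beyond the participating offices. The loss is then smaller, as the first table shows, but its direction stays the same.

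**Stronger readings to avoid.** A reader might infer that the check can almost never detect selective attendance. That fits differences near 0.2 SD or attendance of 45% against 55%, but not larger ones. A reader might also see a second error in the shrunken contrast (1−f)Δ. It is a legitimate measure of how far participants depart from the target population, and with its correct standard error it gives the same z as participants against non-participants; only the standard error is wrong. Finally, the article nowhere says that a non-significant result will be reported as proof of representativeness.

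**Conclusion.** Wrong as written on the natural reading, and minor. The comparison uses overlapping groups with tests for separate ones. At the planned 50% attendance the real level falls from 5% to about 0.07%, and power falls from 80% to about 28%. Large differences in age or attendance would still show; small to moderate ones would often be missed, more so within one group of 206 than in the pooled 412. The figures assume that the named tests are applied to age and occupation, that the study population is about half of those invited, that SDs are equal, and that clustering by physician can be ignored for this check. The check is ancillary: the primary outcome, its multilevel model and the sample size are untouched, and a conservative test raises no false alarm.

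**What to change.** Replace the comparison with one between participants and invited non-participants (invited minus participants) on age and occupation, and report the differences with 95% confidence intervals instead of relying on a p-value. At 206 against 206 the half-width for age is about 1.96 × sqrt(2/206) = 0.19 SD; at 103 against 103 it is 1.96 × sqrt(2/103) = 0.27 SD. The reader can then see how much selection the data exclude.

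Where the data allow, separate non-attenders from attenders who were ineligible or did not consent, since subtraction alone mixes them and does not isolate selective attendance. If the sponsor prefers to keep the contrast with all invited workers, it should use the standard error s × sqrt((1−f)/(fN)).

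The cost is one sentence. Age and occupation of all invited workers are already needed for the planned comparison; only the split by reason for non-participation might need an extra item recorded.

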### Objectives

We hypothesise that the job-specific WHS will influence workers who attend it to undertake preventive actions. Moreover, we hypothesise that based on the job-specific WHS, OPs will advise more preventive actions in total and more job-specific (compared with general health) preventive actions. The objective of this paper is to describe the study protocol used to evaluate the job-specific WHS and to test these hypotheses.

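### The plan asserts clustering by OP but gives a clustered model only for binary data; the one test it names for continuous outcomes is a t-test that ignores the OP

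*Protocol article*

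**What the plan says.** The first paragraph of the Statistical analysis section lists comparisons of baseline characteristics between groups, of workers lost and retained, and of participants with everyone invited: "Moreover, the age and occupation of the study population at baseline and target population (all invited by the OHS) will be compared". It closes with "Differences in continuous outcome measures will be tested with an independent samples T-test, differences in proportions will be tested with a Chi-Square test".

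The second paragraph turns to effectiveness: "The effectiveness of the job-specific WHS on the primary and secondary outcome measures will be analysed on the individual level". It gives the reason for a multilevel analysis, "Workers with the same OP tend to be more homogeneous than workers with different OPs", and concludes that "a two-level logistic regression model with workers at level 1 nested within OPs at level 2 will be used to analyse the binary data". No model is named for data that are not binary.

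The Secondary outcomes section includes outcomes that are not binary: "the number and type of preventive actions (job-specific or general health) advised by the OP", and "the number and type of preventive actions undertaken (job-specific or general health) by the worker and iv) work ability". One of them carries a stated hypothesis. The Objectives section expects that "OPs will advise more preventive actions in total and more job-specific (compared with general health) preventive actions".

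The section Sample size and assignment allows for the same clustering. It uses an ICC of 0.01, about 15 workers per OP, a design effect of 1.14 and 86 workers per group over at least 6 OPs.

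**The concern.** The reason given for the two-level model applies to every outcome measured on workers, whatever its scale. The remedy is confined to binary data, and the only test named for continuous outcomes treats workers as independent. The intervention is assigned by office, so each OP's patients are all in one arm, and differences between OPs enter the group contrast directly. A worker-level t-test leaves that component out of the standard error.

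At stake are the secondary outcomes on a continuous or count scale. The number of actions advised matters most. It bears on the second study hypothesis and it is the OP's own behaviour, so correlation within an OP may well exceed the 0.01 assumed for what workers do.

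Work ability raises a smaller, related issue. It is obtained at the baseline examination in both arms. A plain comparison of follow-up values would ignore that baseline value and, in a nonrandomised study, keep any initial difference between the arms.

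**Working it through.** **Inputs from the protocol article** (Sample size and assignment; Statistical analysis): 75 workers per group before adjustment, ICC 0.01, about 15 workers per OP, at least 6 OPs per group, two-sided significance level 0.05. ICCs above 0.01 are assumptions; the document gives none.

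**The plan's own figure.** Design effect DE = 1 + (m − 1) × ICC = 1 + 14 × 0.01 = 1.14. Adjusted size = 75 × 1.14 = 85.5, rounded up to 86. Both figures reproduce. Also 86/15 = 5.7, which agrees with 6 OPs.

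**Effect of ignoring the OP.** The worker-level standard error is too small by a factor √DE. The true two-sided error of a nominal 5% test is therefore 2 × (1 − Φ(1.96/√DE)). With m = 15:

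| ICC | DE | √DE | 1.96/√DE | True error, formula | True error, simulated |
|---|---|---|---|---|---|
| 0.01 (plan) | 1.14 | 1.068 | 1.836 | 0.066 | 0.067 |
| 0.02 (assumed) | 1.28 | 1.131 | 1.732 | 0.083 | not run |
| 0.05 (assumed) | 1.70 | 1.304 | 1.503 | 0.133 | 0.132 |
| 0.10 (assumed) | 2.40 | 1.549 | 1.265 | 0.206 | 0.202 |

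The simulation used 2 arms of 6 OPs with 15 workers each, a normal outcome and 20,000 runs per ICC. With m = 86/6 = 14.3 instead of 15, the formula gives 0.066, 0.082, 0.129 and 0.199.

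**Few clusters.** With 6 OPs per arm, a comparison of OP means has 2 × 6 − 2 = 10 degrees of freedom. In the same simulations a t-test on OP means kept its level, at 0.048 to 0.050 for every ICC tried. A statistic of 1.96 has p = 0.05 under the normal distribution but p = 0.078 on 10 degrees of freedom. A mixed model that refers its test to the normal distribution could therefore still give p-values that are too small.

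**The case against.** The strongest reply is about placement. The t-test sentence ends the paragraph on baseline, attrition and representativeness comparisons, and effectiveness is taken up only in the next one. On that reading the t-test never touches an effectiveness outcome. What remains is a model not named for some secondary outcomes, which a condensed article may leave to a fuller document.

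The reading is possible, but it does not settle the matter. The paragraph calls its baseline variables *characteristics*. The disputed sentence speaks of *outcome measures*, the term that the next sentence uses for the primary and secondary outcomes. The paragraph also opens by mentioning the primary and secondary parameters. Even on the narrow reading, the text limits to binary data a remedy whose stated reason is general.

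Several stronger readings are tempting but unsupported:

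- **That the plan assigns counts to the t-test.** The section does not mention counts. This is an inference from the absence of any other test.
- **That the p-values will be too small.** This follows only if the t-test is in fact used for these outcomes.
- **That the chi-square half puts the primary analysis in doubt.** Binary effectiveness data are expressly given the two-level model. This also covers the proportion of workers with suggested actions.
- **That the inflation is known to be large.** At the only ICC in the document it is modest. A higher value for actions advised is plausible but not documented. The plan also says at least 6 OPs. With 8, say, clusters would average 86/8 = 10.75 workers, and DE at an assumed ICC of 0.05 would be 1 + 9.75 × 0.05 = 1.49 instead of 1.67.
- **That the plan discards baseline work ability.** The article does not say whether follow-up values or changes would be compared. Adjustment is worth specifying, but no stated error is being corrected.

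**Conclusion.** The point holds as an inconsistency in the wording that affects secondary outcomes only; its severity is moderate. The section asserts clustering by OP and the sample size allows for it, yet the only test named for continuous outcomes ignores it and no clustered method is given for non-binary outcomes.

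If the t-test is applied to them, the true error is about 6.6% instead of 5% at the plan's ICC, with the standard error understated by about 7%. It is about 13% and 20% at assumed ICCs of 0.05 and 0.10. These figures rest on about 15 workers per OP, about 6 OPs per arm, and treatment that does not vary within an OP. The simulation further assumes a normal outcome, so for counts the figures are a guide only. The primary outcome already has a two-level model and is untouched.

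**What to change.** 1. State that the t-test and chi-square sentence covers only the baseline, attrition and representativeness comparisons.
2. Analyse work ability with a two-level linear mixed model, OP as random effect, adjusted for baseline work ability. Confirm first that the same score is available at baseline in both arms.
3. Analyse the numbers of actions advised and undertaken with a two-level Poisson or negative binomial model, OP as random effect.
4. Use small-sample degrees of freedom in these models, or analyse OP means, because only about 6 OPs per arm are planned.
5. Keep the planned two-level logistic model for all binary effectiveness outcomes.

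The cost is analysis wording. No further data are needed, and generalised linear mixed modelling is already planned. Confidence intervals for the non-binary outcomes will be somewhat wider: by the table above, about 7% at an ICC of 0.01 and about 30% at an assumed 0.05, before the further widening from the smaller degrees of freedom.
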